## Abstract

**Background:**

The redislocation rate of conservatively treated patella instability is high. One of the leading surgical strategies is medial patellofemoral ligament reconstruction. Over-tensioning is one of the most challenging complications in static medial patellofemoral ligament reconstruction as the graft used for reconstruction is isometric and the anatomical MPFL is a mostly dynamic structure. As an alternative to established static reconstruction techniques, dynamic graft techniques have been introduced for stabilizing the patella with the aim of providing a more physiological reconstruction of the medial patellofemoral ligament. To date, data on clinical outcomes are scarce and on biomechanical outcomes of the dynamic MPFL reconstruction are lacking. Here, we present the protocol of a randomized clinical trial for comparing clinical and biomechanical outcomes of dynamic versus static medial patellofemoral ligament reconstruction.

**Methods:**

This study is a prospective, single blinded, randomized, multicenter, multimodal (clinical and biomechanical) clinical trial. Patients with recurrent patella dislocation requiring isolated MPFL reconstruction will be recruited and randomized to the dynamic or static reconstruction technique. Participants will be followed up for 2 years with a total of five follow-ups. Preoperative magnetic resonance imaging, upright radiographs, surgical reports and patient records will be evaluated, and clinical and functional outcomes will be measured. Patient-reported knee function and anterior knee pain as assessed with the Kujala score will serve as primary outcome. For biomechanical outcome, pre- and postoperative evaluations will be performed to assess isokinetic muscle strength, gait asymmetry, joint kinematics and kinetics, and timing of muscle activity.

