## Methods/design

### Specific aims

The dynamic MPFL reconstruction is a muscle transfer procedure, and we assume that the function and timing of the gracilis muscle activity will change after dynamic MPFL reconstruction. We will compare longitudinal clinical and biomechanical outcomes (Table 1) between two major existing techniques: static reconstruction technique according to Schöttle et al. [20] and dynamic reconstruction technique according to Becher et al. [29].

**Table 1 Tab1:** Procedures summary

Project period	Pre-hospitalization/Screening	Hospitalisation	Follow-up				
Assessment	1	2	3	4	5	6	7
Time	Day 0	Length of stay	6 weeks ± 2 weeks	12 weeks ± 3 weeks	6 months ± 4 weeks	12 months ± 4 weeks	24 months ± 4 weeks
Diagnostics (X-Ray, MRI as indicated)	x						
Informed Consent (Surgery and study)	x						
In-/Exclusion Criteria	x						
Pre-op. Physical examination	x	x (Day 0)					
Data to be provided by the treating clinician							
Intervention (CHOP Code)		x (Day X_1_)					
Complications		x (Day 0-X_2_)	x	x	x	x	x
Physical examination	x	x	x	x	x	x	x
Data to be extracted from routine records							
Demographics		x (Day 0)					
Medical history and medication		x (Day 0)					
Radiographic parameters	x						
Length of stay		x (Day 0)					
Complications		x (Day X_2_)					
Data to be collected by the study nurse in cooperation with the patient							
Kujala, Tegner, Lysholm score, Banff-score		x (Day 0)	x	x	x	x	x
Patient satisfaction		x (Day X_2_)	x	x	x	x	x
End of rehabilitation/end of physiotherapy			x	x	x	x	x
Data to be collected at the Functional Biomechanics Laboratory in cooperation with the patient							
Isokinetic muscle strength	x					x	
Gait analysis	x					x	

#### Specific Aim 1

Compare the clinical outcome of dynamic and static MPFL reconstruction.

#### Hypothesis 1

Patients with dynamic MPFL reconstruction will report equal or better patient reported outcomes compared to patients with static MPFL reconstruction, as assessed with the Kujala score [35] (primary outcome), Banff-II-score [36], IKDC-2000 [36] and the EQ-5D-5L [37]. Patients with dynamic MPFL reconstruction will have comparable redislocation rates. The few studies published to date [29, 38] show good or better clinical results with the dynamic MPFL reconstruction.

#### Specific Aim 2

Evaluate and compare the biomechanical outcomes of dynamic and static MPFL reconstruction.

#### Hypothesis 2

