## Clinical trial protocol

Data of the patients will be collected pre- and postoperatively, and all patients will be in contact with the study staff for 2 years (Fig. 2). All patients fulfilling the inclusion criteria will be enrolled consecutively, thus avoiding selection bias. Participants will be followed up for 2 years with a total of five follow-ups at 6 weeks, 12 weeks, 6 months, 12 months and 24 months. Preoperative magnetic resonance imaging (MRI), upright radiographs, surgical reports and patient files will be evaluated. Patients who fulfil the inclusion criteria but refuse participation will be documented in a separate screening log.

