#### Statistical analysis

The study involves a series of quantitative outcomes and different types of hypotheses. Hypotheses about differences between patients treated with dynamic or static technique will be addressed by describing and visualizing the distribution of the corresponding variables in each patient group and by quantifying the group differences by the difference in mean values with 95% confidence intervals and p-values. Hypotheses concerning the association between two variables will be addressed by visualizing the joint distribution of variables in scatter plots and quantifying the association by partial correlations coefficients with 95% confidence intervals. Hypotheses concerning a change over time will be addressed by visualizing the distribution of individual differences and quantifying the change over time by the mean difference with 95% confidence intervals and p-values. Hypotheses concerning the association in change over time between two variables will be addressed by visualizing the joint distribution of differences in scatter plots and quantifying the association by correlations coefficients with 95% confidence intervals. In addition, the relation to baseline values will be examined. Patient characteristics will be tabulated for each patient group.

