#### Sample size calculation

We based our sample size calculation on the primary outcome, the Kujala score. To date, no high-quality study (randomized trial) on the difference in change in Kujala score between dynamic and static MPFL reconstruction is available. However, in a prospective randomized control trial, Kang et al. [56] compared two different tensioning techniques for static MPFL reconstruction. They reported an effect size of 7.8 for the improvement in the Kujala score for both groups and a group difference in change in Kujala score of 1.9. Based on biomechanical considerations, we expect a larger improvement in patients stabilized using the dynamic MPFL reconstruction. Assuming a 3.8-point improvement in the Kujala score in patients with dynamic MPFL reconstruction compared to patients with static MPFL reconstruction, 54 patients (27 per group) are required to detect a significant difference in change in Kujala score between the two groups with 80% power at a significance level of 5%. We expect a dropout rate of about 10%, and will thus we will target a study cohort of 60 patients (30 per group).

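### The Kujala score is the primary outcome and is measured at five follow-ups, but no visit is named for the single 5% test, so the stated significance level is not protected

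*Protocol article*

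**What the plan says.** The Abstract (Methods) names the outcome without a visit: "Patient-reported knee function and anterior knee pain as assessed with the Kujala score will serve as primary outcome". Hypothesis 1, under Specific aims, names the Kujala score as primary and is also undated: "Patients with dynamic MPFL reconstruction will report equal or better patient reported outcomes compared to patients with static MPFL reconstruction".

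The Clinical trial protocol section gives "a total of five follow-ups at 6 weeks, 12 weeks, 6 months, 12 months and 24 months". In Table 1, the row "Kujala, Tegner, Lysholm score, Banff-score" is marked at Day 0 and at every one of those follow-ups.

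The Sample size calculation describes one comparison. It starts from "Assuming a 3.8-point improvement in the Kujala score in patients with dynamic MPFL reconstruction compared to patients with static MPFL reconstruction" and asks for 54 patients to "detect a significant difference in change in Kujala score between the two groups with 80% power at a significance level of 5" per cent. It names no end visit for the change. The 10% dropout that raises 54 to 60 has no visit either.

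The Statistical analysis section handles group differences by "quantifying the group differences by the difference in mean values with 95% confidence intervals and p-values". It specifies no visit, no model that combines visits, and no order or multiplicity rule among them. The Background mentions only a two-year horizon for the comparison. By contrast, the Biomechanical assessment section fixes those outcomes at one year after surgery.

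**The concern.** A primary outcome is a variable at a time. Here the variable is fixed and the time is not. The sample size section powers one test, and the data collected allow five versions of it. Nothing in the article says which version counts.

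Two things are at stake. First, the 5% level holds only if the visit is chosen independently of the results. If the choice can follow the results, the chance of a false difference rises. Second, the visits are different estimands. A difference at 6 weeks and a difference at 24 months are separate findings, and the same data could show one without the other. The target difference and the dropout allowance also cannot be judged without a visit, because both may differ between 6 weeks and 24 months.

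**Working it through.** **Step 1: the plan's own figures.** Inputs from the Sample size calculation are a difference of 3.8, 5% significance (taken as two-sided, to match the 95% intervals), 80% power, 27 per group and 10% dropout.

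- Dropout: 54 / 0.90 = 60. This reproduces.
- The 27 per group cannot be reproduced forwards, because the article states no standard deviation (SD) of change. Solving backwards from n = 2 × SD² × (1.960 + 0.842)² / 3.8² with n = 27 gives SD = 3.8 × √(27/2) / 2.802 = 4.98 (4.89 with the t distribution). This SD does not enter the error rates in steps 2 to 4.

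**Step 2: upper bound.** With five independent two-sided 5% tests and no true difference, P(at least one significant) = 1 − 0.95⁵ = 0.226.

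**Step 3: correlated visits.** Let Z₁ to Z₅ be the test statistics at the five visits, jointly normal with mean 0 and correlation matrix R. The quantity wanted is P(max |Zⱼ| > 1.96). The article gives no R, so two structures were simulated with 2 million draws per setting. In the exchangeable structure every pair of visits has correlation r. In AR(1), visits k steps apart have correlation rᵏ.

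| r (assumed) | Exchangeable | AR(1) |
|---|---|---|
| 0.5 | 18.2% | 20.1% |
| 0.6 | 16.7% | 18.8% |
| 0.7 | 14.9% | 17.2% |
| 0.8 | 12.7% | 14.9% |
| 0.9 | 10.2% | 11.9% |

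A check with t-tests at 27 per group and exchangeable correlation of 0.5, 0.6, 0.7 and 0.8 gave 18.6%, 16.8%, 15.0% and 13.0%. The range across all settings, including independence, is about 10-23%.

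**Step 4: one direction only.** Counting only false findings in favour of the dynamic technique, the exchangeable rate is 9.1% at r = 0.5 and 6.4% at r = 0.8, against a nominal 2.5%.

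**Step 5: after the fix.** One pre-named visit, or one pre-named contrast, has a two-sided error of 5%. Naming it does not itself change 54 evaluable or 60 enrolled. Keeping all five visits as primary with Bonferroni (1% each) and the back-solved SD of 4.98 would need 2 × 4.98² × (2.576 + 0.842)² / 3.8² ≈ 40.2, so 41 per group. That is 82 evaluable and 82 / 0.90 = 91.1, so 92 enrolled.

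**The case against.** The strongest objection is that this is an article. The ethics-approved full protocol and any statistical analysis plan are not at hand, and either may name the visit. That is true, so the point is limited to what the article fixes. It still stands, because the time point belongs to the definition of the primary outcome and is not a modelling detail. The article powers a test on that outcome, and it does give a time point for the biomechanical outcomes.

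A second objection is that nothing says five tests will be run or that the best one will be chosen. This also stands. The sample size section describes one comparison, and the analysis section gives generic rules by type of hypothesis. A reader might infer that the type I error of this trial is 13-18% and not 5%. The article does not support that. The rate arises only if any significant visit may become the primary result, which the text leaves possible but does not announce.

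A third objection concerns Hypothesis 1. A reader might take the inflated rate as the chance of wrongly confirming it. It is not. The hypothesis says the dynamic technique is at least as good as the static one, and under the simulated null of no difference that statement is true. The 10-23% belongs to the two-sided difference test in the sample size section.

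Finally, equal correlation is doubtful for visits spaced from 6 weeks to 24 months. The figure should therefore be read as a range.

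**Conclusion.** The point holds. The article identifies the primary variable but not the primary test, because the visit is missing wherever the Kujala comparison is described. The 5% level is therefore unprotected, which is not the same as broken.

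If the visit can be chosen after seeing results, the two-sided false-positive rate for a difference is about 10-23%, and 13-18% at exchangeable correlation 0.5-0.8. This rests on an assumed correlation, five two-sided 5% tests and free choice among them. If the visit is chosen blind to the data, the rate is 5%.

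A reader might also infer that the 54 patients and 10% dropout already refer to the end of follow-up. The sample size section ties them to no visit, so that cannot be assumed. The gap should be closed before unblinding. It does not invalidate the design.

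**What to change.** Before any unblinded look at the data:

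1. Name one visit as primary. The 24-month visit is a natural candidate because it ends follow-up and matches the horizon in the Background, but the choice is for the investigators.
2. Estimate the arm difference at that visit, adjusted for baseline Kujala, which is already collected, and for centre, because the randomisation list is generated per centre. A contrast from a repeated-measures model of all five visits is one way to do this. It is an option and not a condition for closing the gap.
3. Report the other four visits as supportive.
4. Check whether the 3.8-point difference and the 10% dropout suit the chosen visit, and restate them if they do not. Do not simply declare that they refer to it.

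The cost is a few sentences in the outcome, sample size and analysis sections, with no new data. The sample size changes only if step 4 shows that an assumption does not fit. The downside is that an effect seen only at another visit becomes supportive.

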**Discussion:**

The results of the study will clarify whether the reported surgery success for patella stabilization via dynamic MPFL reconstruction is due to muscle contraction or to the passive tenodesis effect combined with clinical outcome measures. With this study, we will provide much needed information on knee biomechanics after dynamic versus static MPFL reconstruction to provide evidence to support orthopedic surgeons in evidence-based decision-making in their quest for surgical techniques most favorable for their patients.

*Trial registration* The study protocol was registered at clinicaltrials.gov (NCT04849130). Registered 19 April 2021, https://clinicaltrials.gov/ct2/show/NCT04849130.

## Background

High joint reaction forces in the patellofemoral joint of up to several times body weight [1, 2] are reflected in patellar cartilage being the thickest in the body with a patellar cartilage thickness of up to 7.5mm [3]. Articular cartilage damage is common, with 44.6% cartilage lesions of the patellofemoral joint reported in knee arthroscopies [4]. The pathogenesis of these lesions may result from acute trauma or altered joint loading due to patella instability. After patella dislocation, the incidence of acute osteochondral or chondral injuries is up to 95% after initial patella dislocation [5]. Moreover, chronic cartilage damage has been described at 13-year follow up with patellofemoral osteoarthritis in 22% in patellar instability knees compared to 11% in contralateral healthy knees [6].

Misshaped structures such as a high riding patella (patella alta) [7] or trochlear dysplasia [8] are risk factors for patella instability. The medial patellofemoral ligament (MPFL) has been shown to be the main dynamic stabilizer of the patella against lateral translation [9], especially when the patella has not yet engaged in the trochlear groove (knee flexion < 30°) [10]. After initial patellar dislocation, the MPFL is injured in 94% of the cases [11]. Because the redislocation rate of the patella after conservative management reaches up to 67% [12, 13] most authors recommend surgical management of these cases, and a variety of surgical procedures has been developed [14].

The leading surgical strategy is to stabilize the patella through a reconstruction of the insufficient or disrupted soft tissue of the MPFL. This is necessary in recurrent patella dislocations and in particular cases of first patella dislocations such as patients with severe anatomical risk factors [15]. The anatomical risk factors should be corrected as well because these patients have an increased rate of revision surgeries, re-dislocations and persistent joint instability compared to those without anatomical risk factors [16]. Moreover, a prolonged time from dislocation to surgery appears to be associated with increased risk of re-dislocations [17]. To date, experts disagree regarding the treatment of complex patella instability [18]. In MPFL reconstruction, a graft (harvested autologous tendon or allograft) intended to stabilize the patella is placed using tunnels, screws, and/or anchors. While the use of interference screws versus suture anchors for isolated MPFL reconstruction has been shown to have similar clinical outcomes, the use of screws was associated with slightly higher complication rates [19]. One established procedure is the static MPFL reconstruction according to Schöttle et al. [20] (Fig. 1), who use the autologous gracilis tendon to stabilize the patella with a static reattachment to the femur. Despite good long-term outcomes of the static MPFL technique [16, 21–23] for up to 4 years, there remains a risk of malpositioning or over-tensioning the graft [24]. While too low graft tension leads to recurrent instability and failure, too high graft tension can lead to persistent knee pain and result in higher patellofemoral pressure, which may ultimately lead to patellofemoral joint degeneration and osteoarthritis [22, 25–27]. Over-tensioning is one of the most challenging complications—even in clinically adequately placed MPFL reconstructions—as the graft used for reconstruction is isometric, whereas the anatomical MPFL is a mostly dynamic structure [28] being tight in extension and early flexion and nearly isometric beyond 30° of flexion [24].

**Fig. 1 Fig1:**
[figure not shown]
Native anatomy, static and dynamic MPFL reconstruction

Several studies have addressed the challenges of correct isometric graft tensioning by evaluating the appropriate load and manner of optimal graft tension during surgery and ways of determining the optimal length and elasticity of the graft [24, 26]. As an alternative to static reconstructions, more elastic insertion techniques with soft tissue fixation only have been suggested [29–33] where the static graft is attached to soft tissue allowing small movements. The medial patellotibial ligament (MPTL) is considered as another restraint of patellar stability and often reconstructed as well in soft tissue fixation procedures [33, 34]. Becher et al. [29] have suggested that not only a dynamic insertion but also a dynamic rather than a static graft should be used for stabilizing the patella. They described a fully dynamic MPFL procedure by detaching and reinserting only the distal part of the gracilis muscle to the patella and leaving the proximal tendon attached to its muscle presumably facilitating dynamic adjustment of the patellar position by muscle contraction (Fig. 1). In a retrospective cohort study, Becher et al. [29] reported comparable mean outcomes of static and dynamic MPFL reconstruction are measured by Kujala, Tegner and Lysholm scores with large variability among groups. The advantage of this dynamic graft procedure is an improved physiological reconstruction of the MPFL as a mostly dynamic structure. Moreover, several surgical steps of the static MPFL reconstruction are avoided, and the dynamic MPFL procedure is therefore faster, simpler and more cost effective. While the advantages of shorter and more forgiving surgical technique in the Becher's procedure seem to make it preferable to other techniques, to date high-quality data on clinical and functional outcomes are lacking.

In this prospective, single blinded, randomized, multicenter clinical trial, we will compare clinical and biomechanical outcomes of static MPFL reconstruction according to Schöttle et al. [20] and dynamic MPFL reconstruction according to Becher et al. [29] up to 2 years after surgery.

## Methods/design

### Specific aims

The dynamic MPFL reconstruction is a muscle transfer procedure, and we assume that the function and timing of the gracilis muscle activity will change after dynamic MPFL reconstruction. We will compare longitudinal clinical and biomechanical outcomes (Table 1) between two major existing techniques: static reconstruction technique according to Schöttle et al. [20] and dynamic reconstruction technique according to Becher et al. [29].

**Table 1 Tab1:** Procedures summary

Project period	Pre-hospitalization/Screening	Hospitalisation	Follow-up				
Assessment	1	2	3	4	5	6	7
Time	Day 0	Length of stay	6 weeks ± 2 weeks	12 weeks ± 3 weeks	6 months ± 4 weeks	12 months ± 4 weeks	24 months ± 4 weeks
Diagnostics (X-Ray, MRI as indicated)	x						
Informed Consent (Surgery and study)	x						
In-/Exclusion Criteria	x						
Pre-op. Physical examination	x	x (Day 0)					
Data to be provided by the treating clinician							
Intervention (CHOP Code)		x (Day X_1_)					
Complications		x (Day 0-X_2_)	x	x	x	x	x
Physical examination	x	x	x	x	x	x	x
Data to be extracted from routine records							
Demographics		x (Day 0)					
Medical history and medication		x (Day 0)					
Radiographic parameters	x						
Length of stay		x (Day 0)					
Complications		x (Day X_2_)					
Data to be collected by the study nurse in cooperation with the patient							
Kujala, Tegner, Lysholm score, Banff-score		x (Day 0)	x	x	x	x	x
Patient satisfaction		x (Day X_2_)	x	x	x	x	x
End of rehabilitation/end of physiotherapy			x	x	x	x	x
Data to be collected at the Functional Biomechanics Laboratory in cooperation with the patient							
Isokinetic muscle strength	x					x	
Gait analysis	x					x	

#### Specific Aim 1

Compare the clinical outcome of dynamic and static MPFL reconstruction.

#### Hypothesis 1

Patients with dynamic MPFL reconstruction will report equal or better patient reported outcomes compared to patients with static MPFL reconstruction, as assessed with the Kujala score [35] (primary outcome), Banff-II-score [36], IKDC-2000 [36] and the EQ-5D-5L [37]. Patients with dynamic MPFL reconstruction will have comparable redislocation rates. The few studies published to date [29, 38] show good or better clinical results with the dynamic MPFL reconstruction.

#### Specific Aim 2

Evaluate and compare the biomechanical outcomes of dynamic and static MPFL reconstruction.

#### Hypothesis 2

Patients with dynamic MPFL reconstruction will have less asymmetry in muscle strength and lower extremity gait kinematics and kinetics than patients with static MPFL reconstruction. To date, comparable biomechanical data of the dynamic MPFL reconstruction technique do not exist.

#### Specific Aim 3

Determine whether the reported success for patella stabilization in dynamic MPFL reconstruction is due to muscle contraction or to the passive tenodesis effect.

#### Hypothesis 3

The function of the gracilis muscle will change from a knee flexor with normal activity from pre-swing throughout the entire swing phase to the beginning of the loading response after the surgery to an isolated patella stabilizer, specifically depending on the knee flexion angle. We anticipate that muscle activity will shift more toward the loading response and the whole stance phase at knee angles < 30° of flexion. The capability and efficacy of such muscle transfer procedures have been described for other procedures such as rectus femoris transfer in children with cerebral palsy [39, 40]. The gracilis muscle reaches forces up to 300 N from 0–60° knee flexion [41] indicating that the gracilis muscle is adequate for patella stabilization.

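### Hypothesis 1 claims equal-or-better Kujala scores and comparable redislocation rates, but the trial is sized for superiority and has no margin, so only 'better' can be supported

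*Protocol article*

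**What the plan says.** Three parts of the Protocol article bear on this.

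- **Specific aims, Hypothesis 1.** "Patients with dynamic MPFL reconstruction will report equal or better patient reported outcomes compared to patients with static MPFL reconstruction". The Kujala score is named there as primary outcome. The next claim is "Patients with dynamic MPFL reconstruction will have comparable redislocation rates". Neither statement comes with a margin.
- **Sample size calculation.** The authors write that "we expect a larger improvement in patients stabilized using the dynamic MPFL reconstruction". The planning effect is a 3.8-point advantage for the dynamic technique over the static one, and the resulting number is "54 patients (27 per group) are required to detect a significant difference in change in Kujala score between the two groups". The power behind it is 80% and the test level 5%. Allowing for about 10% dropout brings this to 60. No SD is given, and the sidedness of the test is not stated.
- **Statistical analysis.** Hypotheses about differences between techniques are addressed by "quantifying the group differences by the difference in mean values with 95% confidence intervals and p-values". No rule says what result would count as equal or comparable.

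**The concern.** Equal-or-better is a non-inferiority claim: it needs a stated amount by which the dynamic arm may be worse and still count as equal. Comparable redislocation rates is a claim of the same kind. The sample size serves a different objective, which is to show a difference in favour of the dynamic technique. The primary hypothesis and the sizing objective are both stated in the article, and they do not match.

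What is at stake is how a result near zero may be reported. Such a result is possible: the Background section describes a retrospective cohort with comparable mean scores for the two techniques, and it lists speed, simplicity and cost among the dynamic technique's attractions. If the Kujala difference is small and non-significant, Hypothesis 1 as worded invites the conclusion that the techniques are equal, and nothing in the stated plan could justify that.

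**Working it through.** **1. Reproduce the plan's sample size.** Stated inputs: difference 3.8 points, 27 per group, 80% power, 5% level. The SD is missing, so it has to be solved for, taking the test as two-sided:

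SD = 3.8 × √(27/2) / (1.960 + 0.842) = 4.98 (normal approximation); 4.89 with the t distribution.

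The figure of 54 is thus attainable with an SD of about 4.9, but it cannot be confirmed from the stated inputs. Dropout checks: 54/0.9 = 60. The section also mentions an effect size of 7.8 without defining it. Read as an SD, it would need 67 per group, so it does not reproduce 54. SDs of 7.8 and 10 are used below only as assumptions to show the range.

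**2. What a non-significant Kujala result would mean.** The half-width of the 95% CI is t(0.975; 52 df) × SD × √(2/27) = 2.007 × SD × 0.272.

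| SD | 95% CI half-width (points) | P(non-significant) if dynamic is truly 1.9 worse | P(non-significant) if truly 3.8 worse |
|---|---|---|---|
| 4.9 (implied) | 2.7 | 71% | 20% |
| 7.8 (assumed) | 4.3 | 86% | 58% |
| 10 (assumed) | 5.5 | 89% | 72% |

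The probabilities are from the noncentral t distribution, two-sided 5%, 27 per arm. The 1.9 points is the group difference that the sample size section takes from an earlier randomized trial; 3.8 is the plan's own target.

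**3. Redislocation.** The documents give no expected rate, so event counts are assumed. With 0/27 in an arm, the Wilson upper limit is z²/(n + z²) = 3.84/30.84 = 12.5%. The Newcombe 95% CI for 0/27 versus 0/27 is therefore ±12.5 percentage points. For 2/27 versus 2/27 it is ±16.8. Exact Fisher power for an assumed 5% versus 20% is 19%.

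**4. Could the present size carry a non-inferiority claim on Kujala?** Power at 27 per arm, one-sided 2.5%, true difference 0, noncentrality = margin / (SD × 0.272):

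| Margin (assumed) | SD | Noncentrality | Power |
|---|---|---|---|
| 3.8 | 4.9 | 2.85 | 80% |
| 3.8 | 7.8 | 1.79 | 42% |
| 3.8 | 10 | 1.40 | 28% |
| 1.9 | 4.9 | 1.42 | 29% |

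The 80% in the first row is automatic. The SD was solved from the same 27 per arm and the same 3.8 points, so the row is no independent evidence that the size is adequate.

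**The case against.** Several arguments on the other side are sound.

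- **No stated misuse.** A reader might infer that a p-value above 0.05 will be taken as proof of equality. The article nowhere says so. This is a risk left open by the wording, not a rule in the plan.
- **Hypothesis 1 is not beyond confirmation.** A reader might infer that the trial can never confirm it. A significant result favouring the dynamic arm would show 'better', and hence 'equal or better'.
- **The analysis is not confined to superiority.** The planned 95% CI is the quantity a non-inferiority assessment would use. What is missing is the margin to hold it against.
- **A null result cannot be called the likely outcome.** The authors say they expect a larger improvement with the dynamic technique, and Hypothesis 1 cites studies with good or better results.
- **Redislocation is secondary.** It did not drive the sample size, and low precision for such an event is ordinary in 60 patients. The method for comparing event rates may stand in the full protocol or SAP, so its absence from the article is no fault.

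What remains is narrower. The primary hypothesis and the objective of the sample size are both stated in the article and disagree. The size cannot have been derived from a margin, because the calculation rests on detecting a difference.

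**Conclusion.** The point holds as a mismatch between Hypothesis 1 and the design. The trial can support 'better' on the Kujala score. It states no criterion for 'equal' or 'comparable', and non-significance would supply none. At the implied SD of about 4.9, a true 1.9-point deficit would go undetected about 71% of the time, and more often if the SD is larger. For redislocation, even an event-free trial leaves about ±12.5 percentage points.

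The planned primary estimate and its confidence interval are not invalidated; the fault lies in what may be concluded from them. The Kujala figures rest on a back-solved SD, a two-sided test and 27 evaluable patients per arm. The redislocation figures rest on assumed counts and rates.

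A reader might also infer that non-inferiority could be claimed with no extra patients. That is not supported in general: it holds only at a margin of 3.8 with an SD near 4.9, and the documents justify neither.

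**What to change.** Before unblinding:

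1. Restate Hypothesis 1 as superiority of the dynamic technique on the Kujala score, matching the sample size section.
2. Add one sentence saying that a non-significant difference will not be interpreted as equality.
3. Remove the claim of comparable redislocation rates. Report the risk difference descriptively with a Newcombe or exact 95% CI.

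This needs only wording changes, with no added patients, visits or alpha. The cost is that the trial gives up any claim of equality or comparability.

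If the sponsor does want to claim equal-or-better on Kujala, it should fix a margin and justify it clinically before unblinding. The two-sided 95% CI for dynamic minus static is then read first against minus the margin and then against 0; this fixed sequence costs no alpha. Power must be re-derived with a stated and sourced SD, and the sample size may have to rise. This route is a real trade-off rather than a free correction.
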